# STUDY PROTOCOL (Version 3)

## 1. Project Title:

Building capacity and promoting smoking cessation in the community via “Quit to Win” Contest 2017: a single-blind cluster randomized controlled trial on a combined “cocktail” intervention of brief advice, instant messaging and active referral (AIR) to increase abstinence

## 3. Study sites

The study will be conducted in the community of all 18 District Council districts in Hong Kong.

## 4. Aims of the study

The aim of this project is to promote and evaluate an innovative community-based smoking cessation “cocktail” intervention through the “Quit to Win” Contest organized in all the 18 districts of Hong Kong. The specific objectives of the study are:

- (1) To build capacity in the community on smoking cessation through a train the trainer (TTT) programme;
- (2) To empower the community organizations at the district level to raise the awareness of the harms of smoking and the importance of smoking cessation and reach smokers in the community;
- (3) To test, by a 2-arm RCT, the effectiveness of a combined intervention of face-to-face brief cessation advice (AWARD), semi-personalised interactive instant SC messaging plus active referral to smoking cessation (SC) services (AIR) compared with control subjects among current smokers who joined the contest;

- (4) To evaluate the process and outcome of the recruitment of smokers through the recruitment activities by telephone surveys and qualitative interview
- (5) To conduct qualitative interviews with quitters and non-quitters participated in the RCT to explore their experience on the interventions.

## 5. Outcome measure(s):

### *a) Building up the capacity of community-based smoking cessation intervention*

The outcomes are to increase the knowledge, attitudes and competence of community workers in providing brief smoking cessation intervention.

### *b) To evaluate the process and outcome of the recruitment of smokers in the community*

*Recruitment input:* (i) number of staff/helpers from non-government organizations (NGOs) and The University of Hong Kong (HKU) trained to participate in recruitment and providing community-based smoking cessation services; (ii) number of leaflets and self-help materials distributed in the recruitment activities.

*Recruitment outcomes:* (i) number of recruitment activities organized under the Quit to Win Contest; (ii) number of people, including smokers and non-smokers, reached in all the recruitment sessions; (iv) number of eligible participants enrolled into the Contest;

### *c) Testing the effectiveness of two innovative smoking cessation interventions*

The primary outcome is biochemically validated abstinence at 6-month after baseline. Secondary outcomes include biochemically validated smoking cessation at 3-month, self-reported past 7-day point prevalence abstinence, smoking cessation services use; biochemically validated smoking cessation; and smoking reduction (50% or above reduction in cigarette consumption compared with baseline) at 3- and 6-month. Smoking cessation services use included several indicators: calling a hotline, booking an appointment, smoking cessation clinic attendance, counselling session attendance, and other indicators to be further specified after liaison with the existing services (e.g. services providers' records on services utilization).

## 6. Estimated duration and commencement date

Proposed starting date: 1 June 2017

Proposed study completion date: 30 May 2018  
 Expected final report date: 30 September 2018

## 7. Scientific/historical background

### **Smoking and second-hand smoke in Hong Kong**

Although smoking prevalence is decreasing in Hong Kong, there are still 641,300 daily smokers (10.5%) (Census and Statistics Department, 2016) and half will be killed by smoking (Lam, 2012) which accounts for over 7,000 deaths per year (Lam, Ho, Hedley, Mak, & Peto, 2001). Smoking also accounts for a large amount of medical cost, long-term care and productivity loss of US\$688 million (0.6% Hong Kong GDP) (Census & Statistics Department, 2001; McGhee et al., 2006). Smoking is a highly addictive behavior and it is difficult for smokers with strong nicotine dependence to quit without assistance. On the other hand, reaching and helping the many smokers who have no intention to quit is a challenge, because they are unlikely to seek professional help from smoking cessation services.

### **Previous Quit to Win Contest findings**

The Quit and Win programme provides an opportunity to reach and encourage a large group of smokers to make quit attempt and maintain abstinence. The Quit and Win model posits that smokers participating in the contest will have higher motivation to quit with incentives and better social support (Cahill & Perera, 2011). Studies have found that such quitting contests or incentive programs appeared to reach a large number of smokers and demonstrated a significantly higher quit rate for the quit and win group than for the control group (Cahill & Perera, 2008).

In 2009, we conducted a 3-arm RCT to compare the effectiveness of a 3-minute brief telephone advice, 8 mobile phone (SMS) messages and usual care of smoking cessation self-help booklet (Chan, 2011). More than one thousand participants were successfully recruited in 1.5 months with an overall self-reported quit rate of 21.6% at 6 months. However, the 2 interventions groups did not show a higher quit rate than the control group. In the Quit to Win Contest 2010, we compared the effectiveness of an on-site face-to-face brief smoking cessation advice (intervention) with self-help booklet (control) on quit rate and changes in smoking behavior. Once again, we recruited over one thousand participants in 2.5 months. A marginally significant ( $p = 0.08$ ) higher quit rate was observed in the intervention group (18.4%) compared with

the control group (13.8%) at the 6-month follow-up (Wong & Chan, 2012). The Quit to Win Contest 2012 studied on the effectiveness of the on-site counselling with telephone boosters and health education card was theoretically based on the Health Action Process Approach (HAPA) for the intervention group (Schwarzer, 2008) and the SMS intervention group who received 16 SMS about cessation advice and motivation were compared with the control group. The HAPA suggests that one's intention of behavior change can be fostered by knowing that the new behavior has positive outcomes as opposed to the negative outcomes that accompany the current behavior; and planning (action planning and coping planning) which serves as an operative mediator between intentions and behavior. The quit rates at 3 months were 9.4% (on-site counselling) and 11.5% (SMS) compared with 9.3% in the control group ( $p = 0.93$ ) (Schwarzer, 2008). The Quit to Win Contest 2013 tested the effectiveness of combining competition and short-term monetary incentives to motivate smokers to quit smoking. The overall quit rate was 9.4% (95% CI 7.8%-11.4%). The quit rate for participants who were given prior notice about receiving the monetary incentive (HKD500) upon validated abstinence at the 3-month follow-up was 9.0% (95% CI 6.4-12.6%), which was similar to those who received a delayed notice (Quit rate=10.9%, 95% CI 8.1%-14.7%) and those who did not receive any incentive for abstinence (Quit rate=8.4%, 95% CI 5.9%-11.9%). In 2014, an RCT tested the effectiveness of the cut down to quit (CDTQ) and quit immediately (QI). Smoking reduction or cut down to quit (CDTQ) approach is an important alternative strategy for promoting smoking cessation with several RCTs showing effectiveness (Batra et al., 2005; Carpenter, Hughes, Solomon, & Callas, 2004; Shiffman, Ferguson, & Strahs, 2009). In contrast, a meta-analysis of 10 trials found similar effects in quit rates when comparing quit immediately vs. cut down to quit (15% vs. 14.1%). Some further suggests that quitting gradually was not associated with less success than quit immediately (Lindson-Hawley, Aveyard, & Hughes, 2013). The overall self-reported quit-rate at 6-month is 10.9%. In the last Quit-to-Win Contest in 2015, a 3-armed RCT tested the effectiveness of the active referral and AWARD approaches. The preliminary result presented that the active referral intervention resulted in better quitting.

In QTW Contest 2016, we evaluated the effects of a higher intensity and personalized active referral (HAR) vs. low intensity text messaging (SMS) vs. very brief SC advice (VBA; control group) on encouraging smoking cessation (SC) service use and

increasing the quit rate. HAR included onsite AR, brief advice using AWARD model with a warning leaflet plus a referral card provided, and instant messages as reminders. Text messaging group included brief advice using AWARD model with the same warning leaflet plus the referral card provided and low intensity text messages as reminders. VBA included onsite general brief advices and a 12-page booklet. Findings at 6-month follow-up of this RCT showed that the intervention group with HAR had a significantly higher self-reported quit rate than VBA (the control group) (17.0% vs. 11.2%,  $P = 0.02$ ). Text messaging group also had significantly higher self-reported quit rate than the control group (17.1 % vs. 11.2%,  $P = 0.02$ ).

The seven Quit to Win Contests in Hong Kong recruited over 8,000 smokers from the community. The competition probably helped in boosting up participants' confidence and motivation to quit but additional brief counselling and short messaging services did not significantly increase the quit rate. Lucky draws were included in the past contest for participants who successfully quit (validated by biochemical tests). In accordance with the research direction suggested by the above foreign studies, the forthcoming RCT on Quit to Win Contest will examine the effectiveness of (1) personalized active referral to smoking cessation (SC) services and (2) text messaging on encouraging SC services use to increase quitting compared with control subjects among current smokers who joined the contest.

### **Community participatory model for smoking cessation**

Community-Based Participatory Research (CBPR) is a partnership approach in scientific research that involves the collaboration among community partners and academic researchers throughout the research process (Israel, Schulz, Parker, & Becker, 1998). It has been found effective in enhancing community input, building community capacity, and addressing barriers to health in study participants who have historically been underrepresented in research (Andrews, Newman, Heath, Williams, & Tingen, 2012). Community partners have the capability of mobilizing local social resources and manpower and utilizing their network within the community, which is beneficial to a scientific research involving population-based interventions. To effectively raise the awareness of the contest and recruit as many participants as we can from the community, working with NGOs in the 18 Hong Kong districts with a CBPR model should be one effective way of program implementation.

The challenge of applying the CBPR model in the smoking cessation program is to equip the staff from NGOs and HKU about the related skills and knowledge and maintain the quality of research process and intervention. Process evaluation is a systematic procedure during the delivery of public health interventions to understand how well the program does and to link the progress to outcomes (Centers for Disease Control and Prevention, 2008). In addition to the training programme and briefing session to be provided to the participating NGOs, monitoring and documentation are needed throughout the recruitment and research process so that the quality and integrity of the effort by the involved NGOs can be evaluated.

### **Rationale of using active referral approach**

Smoking cessation substantially increases quit rate and WHO has urged to promote smoking cessation services (World Health Organization, 2015). Smoking cessation services in Hong Kong are under-used with most of the adult daily smokers (79.6%) who had never used smoking cessation services (Census and Statistics Department, 2016). Among these smokers, only 2.4% were willing to use the services. Our previous RCT in previous QTW Contest 2015 evaluated the effects of low-intensity active referral (LAR) vs. very brief general SC advice (VBA) on quitting. LAR included onsite AWARD counselling and collection of smokers' personal contact information for SC services providers to connect with the smokers. Findings at 3-month follow-up of this RCT suggested the LAR intervention resulted in significantly higher self-reported quit rate than VBA in the control group (18.7% vs. 14.0%,  $P < 0.001$ ). Our RCT in previous QTW Contest 2016 evaluated the effects of a higher intensity and personalized active referral (HAR) vs. low intensity text messaging (SMS) vs. very brief SC advice (VBA; control group) on encouraging smoking cessation (SC) service use and increasing the quit rate. Findings at 6-month follow-up of this RCT showed that the intervention group with HAR had a significantly higher self-reported quit rate than VBA (the control group) (17.0% vs. 11.2%,  $P = 0.02$ ). Text messaging group also had significantly higher self-reported quit rate than the control group (17.1 % vs. 11.2%,  $P = 0.02$ ).

However, these SMS-based RCTs could not provide real-time responses from the counsellors, which might weaken the smokers' intention to quit and lower the intensity of social support. In the iQuit RCT, around 18% of smokers from the

intervention group discontinued the programme (Naughton et al., 2014). In the present proposal, we hope to enrich the SMS-based intervention by using WhatsApp or WeChat, which can provide an interactive platform and develop a semi-personalized interactive IM system that can tailor for the smokers according to their characteristics, needs and demand.

Therefore, the present study will examine (1) the effectiveness of regular messages and semi-personalized instant messaging with AWARD brief advice and active referral to smoking cessation (SC) services and (2) explore the use of CBPR model to build capacity and to engage community partners in taking on this important public health issue for sustainability in the community. In addition, a process evaluation will be conducted to assess the effectiveness of the recruitment activity and how it is linked with the overall program outcomes.

## 8. Study design

The present study consists of three phases: (I) provision of the training for smoking cessation ambassadors; (II) process evaluation of participant recruitment activities; and (III) a cluster RCT to test the effectiveness of a combined intervention using brief cessation advice, active referral and semi-personalised interactive instant messaging compared with control subjects among current smokers who joined the contest.

### *8.1 Selection of subjects*

#### *Phase I*

Around 100 staff/helpers from the district partners, COSH, HKU and other parties who will take part in the QTW 2017 will be invited to participate in a brief training programme. The TTT programme will (1) provide staff/ helpers with an overview of the QTW 2017 project; (2) equip them with the knowledge and new simple skills of helping smokers stop smoking in their respective communities; and (3) train them to give brief advice on smoking reduction and use of existing smoking cessation services. The effect of the programme will be evaluated by pre- and post-tests. At least two half-day sessions of training will be held and the following topics will be covered in each session:

- (1) Introduction of COSH;
- (2) Objective and details of the QTW 2017 Campaign;
- (3) Marketing and promotion of smoke-free messages;

- (4) Global tobacco epidemic and control measures, including smoke-free policies and smoking cessation services in Hong Kong;
- (5) Smoking hazards of active smoking, second-hand and third-hand smoke;
- (6) Effectiveness of instant messaging interaction, brief smoking cessation interventions, referral to and use of existing services;
- (7) Brief smoking cessation and reduction advice and counselling skills with case study and sharing; and
- (8) A brief introduction of evaluation using randomised controlled trial (RCT).

## ***Phase II***

About 70 sessions of recruitment and promotion activities will be organised with liaison with COSH aiming to recruit 1,200 participants. Well-trained smoking cessation ambassadors (about 6 per recruitment activity) will be deployed for onsite recruitment, brief intervention (e.g. brief SC advice), monitoring and evaluation. Each recruitment activity will be a study unit of the process evaluation and all the recruitment inputs and outcomes will be documented by a research staff for further analysis.

## ***Phase III***

We use the best study design possible under the constraints of the QTW to evaluate the effectiveness of two new brief interventions. We follow the CONSORT (Schulz, 2010) in the design, implementation and reporting for the proposed cluster RCT. Participants will be recruited in the community of all 18 districts during QTW recruitment activities in Hong Kong.

The cluster RCT has 2 arms: intervention group A (Group A), and control group (Group B). The participants will be randomly assigned to one of the 2 groups based on the session they are being recruited (cluster randomization). Individual randomization at the recruitment site can have several subjects being recruited together at the same time resulting in contamination as some subjects may be exposed to the unintended interventions inadvertently. Based on the method of random assignment of recruitment session, subjects will be allocated according to the randomly selected session to either group. The randomization for group assignment will be generated by the investigators of the project before participant's recruitment

and allocation concealment will be ensured (please refer to “Randomization” for details). We follow the CONSORT (Schulz, Altman, Moher, & Consort Group, 2011) in the design, implementation and reporting for the proposed cluster RCT.

Individual telephone or face-to-face interviews will be conducted on a purposive sample of quitters and non-quitters participated in the RCT after completion of 6-month follow-up to explore their perceptions on the intervention, comments of improvement and factors contributing to the quitting/ non-quitting. The study endpoint (sample size) will be determined by data saturation.

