#### Inclusion criteria

- Hong Kong residents aged 18 or above
- Smoke at least 1 cigarette per day in the past 3 months
- Able to communicate in Cantonese (including reading Chinese)
- Exhaled carbon monoxide (CO) 4 ppm or above, assessed by a validated CO Smokerlyzer.
- Intent to quit / reduce smoking
- Using a cell phone with instant messaging tool (e.g. WhatsApp, WeChat)
- Able to use instant messaging tool (e.g. WhatsApp, WeChat) for communication

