### ***Phase III: Recruit and provide smoking reduction/cessation counselling***

At the recruitment sessions, smoking cessation counsellor will measure the potential participant's level of carbon monoxide (CO) in exhaled air, screen their eligibility for entering the contest, and provide the self-help smoking cessation booklets developed by the Hong Kong Council on Smoking and Health (COSH). Then the counsellor will explain and invite the participants to join the RCT on smoking cessation intervention. Written consent for voluntary participation in the trial will be obtained before administering the baseline questionnaire and delivery of the intervention for the participants.

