### ***8.3 Randomization***

By cluster randomization, all participants recruited in a particular recruitment session (one day may have more than one activity) will be allocated to one of the RCT groups. Block randomization will be used to allocate the recruitment activity into the two RCT groups to ensure the number of recruitment activities for the two RCT groups is similar. The numbers for the permutation in the blocks will be generated with the website <http://www.random.org> (a website for generating random integers), and then merge with the list of all recruitment days.

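### The protocol claims allocation concealment, but the design provides none when individual smokers are enrolled within a session, which leaves a risk of recruitment bias

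*Protocol*

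**What the plan says.** Section 8.1 (Phase III) makes two statements about the sequence: "The randomization for group assignment will be generated by the investigators of the project before participant's recruitment", "and allocation concealment will be ensured". It sends the reader to the randomization section for the details.

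Section 8.3 is that section. It sets the unit of allocation: "all participants recruited in a particular recruitment session (one day may have more than one activity) will be allocated to one of the RCT groups". It then describes block randomization with numbers from a public random-integer website, "and then merge with the list of all recruitment days". It does not say who holds the list, how or when a session's arm is released, or who is kept unaware of it.

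For conduct on the day, Section 8.1 (Phase II) says "Well-trained smoking cessation ambassadors (about 6 per recruitment activity) will be deployed for onsite recruitment", and the same sentence gives these ambassadors the brief intervention as well. Section 8.2 (Phase III) has a counsellor measure exhaled CO and screen for eligibility. It continues: "Then the counsellor will explain and invite the participants to join the RCT on smoking cessation intervention". Written consent comes before the baseline questionnaire and the intervention. One inclusion criterion is "Intent to quit / reduce smoking". Under Non-trial Group, smokers who refuse the trial stay in the contest but are analysed apart from it.

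**The concern.** Randomizing sessions makes the sessions comparable. It makes the enrolled smokers comparable only if enrolment does not depend on the arm. Here the arm is fixed before anyone at the session is approached. If recruiters know it, the way they judge intent, explain the trial or encourage participation may differ between Group A and Group B sessions. Smokers' willingness to join may differ too if they can see what others receive. Intent to quit bears directly on the primary outcome, validated abstinence at 6 months.

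Such a difference arises before the analysis set exists. Counting losses and refusals at follow-up as failures, as Section 8.6 does, leaves it untouched, and a larger sample would not reduce it. A reader who relies on the concealment claim would assume a protection that the design lacks.

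**Working it through.** **1. The claim against its cross-reference.** Section 8.1 promises concealment and says where it is described. Section 8.3 covers the unit of allocation, the blocks, the source of the numbers and the merge with the recruitment days. None of these hides the arm from the people enrolling smokers.

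**2. Can recruiters know the arm?**
- Everyone in a session gets the same arm (Section 8.3).
- The on-site team recruits and gives the brief intervention (Section 8.1, Phase II).
- The arms look different. Group A gets AWARD advice, a warning leaflet and a referral card; Group B gets a few general sentences (Section 8.2, Table 1).

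Whoever treats the first participant knows the arm for the rest of the session.

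**3. How many smokers come later?** Section 8.1 (Phase II) plans about 70 sessions and 1,200 participants: 1,200 / 70 = 17.1 per session. If the first treatment reveals the arm to the whole team, 16 of 17 follow it. If each of about six ambassadors treats one participant before learning the arm (an assumption), 17 − 6 = 11 of 17 still follow.

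**4. The plan's sample size, for context.** Inputs from Section 8.5: p1 = 0.051; RR = 1.83, so p2 = 0.051 × 1.83 = 0.0933; power 80%; 5% significance, taken as two-sided. With pooled variance and no continuity correction:

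n = [1.96·√(2·p̄(1−p̄)) + 0.842·√(p1(1−p1) + p2(1−p2))]² / (p2−p1)², p̄ = 0.0722

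This gives 586 per group, as stated. The planned difference is 0.0933 − 0.051 = 4.2 points.

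**5. Illustration of what a shift would do.** Assume no true effect, 586 per group, no clustering (Section 8.5 takes the design effect as negligible), and a rate in Group A raised by b through selective enrolment. The values of b are assumptions. With q1 = 0.051, q2 = 0.051 + b and q̄ their mean:

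se0 = √(2·q̄(1−q̄)/586), se1 = √([q1(1−q1) + q2(1−q2)]/586)

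type I error = Φ((b − 1.96·se0)/se1) + Φ((−b − 1.96·se0)/se1)

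For b = 0.01, se0 and se1 are both about 0.0134. The two terms are Φ(−1.22) = 0.112 and Φ(−2.71) = 0.003, which sum to 0.115.

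| b (points) | Share of planned 4.2 points | Two-sided type I error |
|---|---|---|
| 0 | 0% | 5.0% |
| 0.5 | 12% | 6.7% |
| 1.0 | 24% | 11.5% |
| 1.5 | 35% | 19.4% |
| 2.0 | 47% | 29.8% |

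**6. What would produce such a shift?** Take b as the gap in quit rate between more and less ready smokers, times the imbalance in readiness between arms. With assumed quit rates of 8% and 3%, a 10-point imbalance gives 0.05 × 0.10 = 0.5 point and a 20-point imbalance gives 1.0 point. The documents supply neither the gap nor the imbalance.

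**The case against.** Several stronger readings are tempting, and the documents do not support them.

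- **That counsellors know the arm before the first consent.** No section says when on-site staff learn it. Knowledge after the first treatment follows from the procedure; earlier knowledge is inference.
- **That one person screens, invites, consents and treats.** Section 8.2 gives CO measurement, screening and invitation to a counsellor, but does not say who takes consent. The ambassadors' duties are listed for the team, not for each member.
- **That less ready smokers can be diverted to the non-trial group.** That group covers refusers and people unable to read or communicate in Chinese. It does not mention smokers screened out on intent. Only the refusal route stands.
- **That the arms will differ.** No motive to enrol differently by arm is documented. Most criteria (age, daily smoking, CO, use of a messaging tool) are largely objective, and the intent criterion also accepts an intent merely to reduce. The unpredictable assignment of sessions may be fully intact.

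The other side can add that recruitment after allocation is inherent in randomizing sessions, which Section 8.1 justifies by contamination. An investigator or senior research assistant also spot-checks every venue (Section 8.2, Phase II). Both are fair. However, the stated aim of the spot checks is consistent delivery, not protection of enrolment. Model covariates may also be settled in a statistical analysis plan that is not shown, so their absence here is not a fault; adjustment is proposed as a partial remedy.

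These arguments narrow the point and lower its severity. They do not supply the concealment step that Section 8.1 says is in Section 8.3.

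**Conclusion.** The point holds as a false design statement together with a risk of recruitment bias. The protocol can claim unpredictable assignment of sessions. It cannot claim concealment at individual enrolment, because recruiters can know the arm for most of a session's smokers, and one entry criterion and the decision to join leave room for selection.

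The size is unknown. Under the assumed shifts of 0.5 to 1.0 point, the type I error would be about 7% to 12% instead of 5%. This illustrates sensitivity and does not estimate the bias. No stated figure changes, and 586 per group stands as calculated. The protocol should be corrected on this point, but the documents do not show that the primary comparison is invalid.

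**What to change.** 1. **Sections 8.1 and 8.3:** replace the concealment claim with what the design provides: unpredictable assignment of sessions, with no concealment at individual enrolment within a session. Have the list held by someone who neither schedules nor staffs sessions, and release each arm only at its session.
2. **Section 8.2, Phase III:** where feasible with the ambassadors already on site, have screening, consent and the baseline questionnaire completed by staff other than those delivering the arm. State that this masks only partly, since recruiters at the same booth may see Group A's leaflet and card after the first participant.
3. **Section 8.6:** include baseline cigarette consumption and past quit attempts in the primary GEE model. Section 8.4 already collects smoking behaviour and quit attempts at baseline. Adjustment deals only with measured differences.
4. **Phase II process form:** report smokers approached, eligible, consented and refusing by arm. Smokers approached and contest enrolments are already recorded, and each session is one arm, so mainly the trial consent and refusal counts are new.

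The cost is a small logistic burden at the sessions, two added counts on a form, and a less favourable but accurate design statement. The sample size does not change.
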